### Interim analyses and trial termination

This clinical trial project plans to recruit 400 patients and conduct an interim data analysis, faithfully reflecting changes in their condition during and after the operation, at the point in which about 200 patients have been enrolled. To improve the trial further, we have established a data monitoring committee that consists of surgical experts, statistics experts and ethics experts, independent of the clinical research team of the project, to weigh the effectiveness and safety comprehensively at the midpoint of the clinical trial according to the data accumulated to date and then make important decisions regarding whether to “continue the trial”, “continue the trial after adjusting the protocol” or “terminate the trial”. The results of the interim analysis will be released to all investigators.

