## Methods: Participants, interventions and outcomes

### Participant selection and randomization

Patients who have a diagnosed middle and lower gastric adenocarcinoma and who underwent laparoscopic-assisted radical resection of distal gastric cancer will be recruited from the 13 hospitals listed in Table 1. To achieve adequate enrolment, all surgeons in the gastrointestinal departments of the cooperating hospitals have been informed of this trial. Patients will be recruited for the study from the gastrointestinal surgery or gastrointestinal surgery outpatient clinic or by referral from the local affiliated hospital. The enrolment period is expected to be completed within 10 months from the beginning of recruitment. A total of 400 eligible patients will be selected and randomly (1:1) enrolled in the ERAS group and the traditional treatment group. Figure 1 shows the test group selection flowchart.

**Table 1 Tab1:** The 13 participating surgical centres

Number	Centre	Department and investigator
1	Affiliated Hospital of Qingdao University	Gastrointestinal Surgery, [name]
2	Shandong Provincial Hospital	Gastrointestinal Surgery, [name]
3	Qilu Hospital of Shandong University	Gastrointestinal Surgery, [name]
4	Qianfoshan Hospital of Shandong Province	Gastrointestinal Surgery, [name]
5	Second Hospital of Shandong University	Gastrointestinal Surgery, [name]
6	Yantai Yuhuangding Hospital	Gastrointestinal Surgery, [name]
7	Weihai Municipal Hospital	Gastrointestinal Surgery, [name]
8	Weifang People’s Hospital	Oncological Surgery, [name]
9	Dongying People’s Hospital	General Surgery, [name]
10	Rizhao People’s Hospital	General Surgery, [name]
11	Qingdao Municipal Hospital	Gastrointestinal Surgery, [name]
12	Jining People’s Hospital	Gastrointestinal Surgery, [name]
13	Weihai Central Hospital	Gastrointestinal Surgery, [name]

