### Sample size estimate

This study adopts the design of a non-inferiority test, and the calculation of sample size is based on the following historical data and assumptions. Previous studies have shown that the overall 3-year survival rate for patients with gastric cancer is about 50% [5]. The centre followed patients who underwent radical resection of gastric cancer under the management of ERAS from 2011 to 2014, and the 3-year survival rate was about 65% [21]. Given that patient selection will require 10 months, the median follow-up time should be about 3 years, and therefore the non-inferiority threshold is set to 1.33, according to a 1:1 random ratio. Given a significance level of α = 0.05 (bilateral) and test efficiency of 1 − β = 80%, the withdrawal rate of either branch group should be 10% and thus the total sample requires at least 400 patients (200 in the test group and 200 in the control group).

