## Discussion

The core of the ERAS concept is to use perioperative optimization measures based on evidence-based medicine to reduce surgical trauma and the stress response and to promote postoperative recovery. This concept has subverted the thinking and principles of perioperative management formed over the past hundred years and has created a new concept of rehabilitation. The ERAS pathway not only can improve the early clinical outcomes of patients with gastric cancer but also (it is hoped) can improve the survival rate of patients. This study is a prospective, multicentre, open, randomized controlled clinical trial that aims to provide important evidence support to achieve this goal.

In recent years, many international large-scale gastric surgery centres have begun to explore the ERAS pathway for gastric cancer. The application of the ERAS pathway in the perioperative management of gastric surgery has been repeatedly proven to be able to reduce postoperative complications, shorten postoperative hospital stays, relieve postoperative pain and reduce total hospitalization costs [11, 22]. Unfortunately, the ERAS pathway has limited research on improving the survival of patients with gastric cancer. Current observational studies have shown a significant association between ERAS compliance and colorectal cancer survival. In patients with more than 70% adherence to ERAS interventions, the risk of 5-year cancer-specific death was lowered by 42%, hazard ratio 0.58 (0.39–0.88, Cox regression), compared with all other patients (≤70% adherence) [17]. At present, one mechanism of the ERAS pathway to improve this result is to reduce the surgical stress response [9]. Some studies have shown that perioperative stress not only can affect tumour recurrence [23, 24] but also can stimulate dormant micrometastases and minimal residual cancer [25–27]. In addition, under the ERAS management mode, the immune function after operation can be better preserved. Studies have shown that surgery is related to short-term immunosuppression after surgery [27]. Pro-inflammatory cytokines released after surgery, such as TNF-α and transforming growth factor-beta (TGF-β), have also been shown to stimulate tumour cell adhesion [28, 29]. Patients managed by the ERAS pathway show better preservation of cell-mediated immunity and immune function and a lower stress response, thereby inhibiting tumour recurrence and metastasis and prolonging patient survival [30, 31].

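### Interim results will be released to all investigators of an open trial with about half the patients still to enrol, after a look that says little about survival

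*Protocol article*

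**What the plan says.** All of this is in the protocol article.

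- **Timing.** Under Interim analyses and trial termination, one interim analysis is planned "at the point in which about 200 patients have been enrolled", out of 400.
- **Who looks, and at what.** A data monitoring committee, "independent of the clinical research team of the project", is "to weigh the effectiveness and safety comprehensively at the midpoint of the clinical trial". It may "make important decisions regarding whether to" carry on unchanged, carry on under an amended protocol, or stop.
- **Who learns the results.** The section ends: "The results of the interim analysis will be released to all investigators". No restriction on content or recipients is stated.
- **Masking.** The Discussion says: "This study is a prospective, multicentre, open, randomized controlled clinical trial".
- **Recruitment.** Under Participant selection and randomization: "The enrolment period is expected to be completed within 10 months from the beginning of recruitment".
- **Endpoint.** Study endpoints makes 3-year overall survival (OS) and disease-free survival (DFS) the main comparison. Complications, readmission, 30-day mortality, length of stay and costs are secondary.

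**The concern.** An independent committee exists so that the people who recruit and treat patients do not know how the arms compare while the trial is running. Here the same paragraph creates the committee and then passes its results to those people. This is a stated rule, not a detail left to another document.

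The setting makes it matter. Investigators know every allocation. The arms differ in feeding, mobilisation, tubes, drains and analgesia (Table 2), which a team can shift without any visible protocol breach. Strengths and limitations says the cooperating centres all belong to a gastric cancer ERAS group. A team that has seen interim results favouring ERAS may become selective about whom it enrols, manage controls more like ERAS patients, or discharge ERAS patients more readily. Sample size estimate describes a non-inferiority design, and in such a design convergence of the arms makes the conclusion easier to reach. Bias of this kind cannot be repaired in the analysis.

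The second question is what the look can tell the committee about the main endpoint, since it is triggered by enrolment and not by events.

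**Working it through.** The article gives no number of deaths for the interim or the final analysis, so there is no stated figure to reproduce. The total of 400 is taken as given.

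**Inputs**
- 3-year survival of 50% (historical) and 65% (under ERAS), from Sample size estimate
- 400 patients, 1:1, with 10% withdrawal, from the same section
- 10-month enrolment, from Participant selection and randomization
- Assumed: exponential survival, uniform accrual, and no lag between the 200th enrolment and the data cut

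**Position at the look**
- Accrual is 400 / 10 = 40 per month, so 200 are enrolled at month 200 / 40 = 5 and 200 remain.
- Mean follow-up of those enrolled is 2.5 months. Ignoring deaths, that is 200 × 2.5 = 500 patient-months out of 400 × 36 = 14,400, or 3.5%.

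**Expected deaths at the look**
- Monthly hazards: −ln(0.50)/36 = 0.01925 and −ln(0.65)/36 = 0.01197.
- With n = 100 per arm and a = 5 months, expected deaths = n × [1 − (1 − exp(−λa)) / (λa)].
- Control: λa = 0.0963, giving 4.66. ERAS: λa = 0.0598, giving 2.93. Total 7.6, about 8.

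**Sensitivity.** With a lag of L months to the data cut, expected deaths among these 200 = n × [1 − exp(−λL) × (1 − exp(−λa)) / (λa)].

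| Scenario | Deaths |
|---|---|
| Both arms 65% at 3 years, no lag | 5.9 |
| 50% and 65%, no lag | 7.6 |
| Both arms 50% at 3 years, no lag | 9.3 |
| 50% and 65%, 1-month lag | 10.6 |
| 50% and 65%, recruitment filling the whole window in Trial status (half at about 7.3 months), no lag | 11.0 |
| 50% and 65%, 3-month lag | 16.4 |

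**Share of the final information**
- Deaths by 36 months: 200 × 0.50 + 200 × 0.35 = 170, or 170 × 0.9 = 153 after a crude 10% loss.
- The look has 7.6/170 = 4.5% to 7.6/153 = 5.0% of these. With a 3-month lag it has about 10% (16.4/170).

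**Precision**
- With 8 deaths, the 95% interval for the hazard ratio is the estimate divided and multiplied by exp(1.96 × 2/√8) = 4.0. With 16.4 deaths the factor is exp(1.96 × 2/√16.4) = 2.6.
- The 50% and 65% rates imply a hazard ratio of ln(0.65)/ln(0.50) = 0.62. Power to detect it with 8 deaths at two-sided 0.05 is about 10%.

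No DFS rate is given, so DFS events cannot be computed.

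**The case against.** **The results may not be comparative.** The article says only that results are released. That they compare the arms is an inference, but a fair one: effectiveness can hardly be weighed without a comparison, and no restriction is stated.

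**Safeguards exist.** Under Data collection and management, nurses record recovery daily, treating clinicians stay out of data collection and independent staff complete the case report form. Discharge criteria are written down. Follow-up is done by a dedicated team on a fixed schedule with imaging. OS is an objective endpoint. These points stand, and they weaken the case for biased complication reporting or recurrence work-up. They do not protect recruitment or control-arm care. Discharge is only partly protected, since the criteria include the patient's willingness to leave and the adequacy of care at home.

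**Fewer patients may remain.** With a 3-month lag and recruitment continuing, 200 + 3 × 40 = 320 would be enrolled and 80 would remain. That narrows the recruitment route but leaves almost all follow-up ahead.

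**The look may concern short-term outcomes.** The section says the interim data describe how patients fare in and after surgery, which points to perioperative results. If so, the sparse deaths matter less. Release then matters more, because differences in complications or length of stay could be clear with 200 patients, and surgeons still treating controls would see them. Against that, the Introduction and Discussion show that the investigators already favour ERAS, so the added influence of release is plausible but cannot be quantified.

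**A stronger reading on type I error is tempting.** A reader might infer that no alpha is reserved for the look and that the final test at 0.05 is therefore inflated. The document does not support this. It plans no interim survival test at 0.05. A stopping boundary may sit in the full protocol, the analysis plan or a committee charter, none of which is shown. At about 5% of the information, an O'Brien-Fleming-type spending rule would use essentially no alpha. All that can be said is that this article states no interim boundary.

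**Conclusion.** The point holds on the release sentence, and that sentence should be changed before the look takes place. It rests on explicit text and on one fair inference, that the results compare the arms. The size of the resulting bias cannot be calculated. Its main routes are recruitment and control-arm care, with discharge decisions partly protected.

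The supporting point, that the look carries little survival information, also holds, with less precision. It rests on constant hazards, uniform accrual and the 3-year rates in the article. Even the longest lag considered leaves the look with only about a tenth of the final deaths. The claim is limited to OS, and no claim is made about type I error.

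**What to change.** Replace the last sentence of Interim analyses and trial termination with:

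> Comparative interim results remain confidential to the data monitoring committee; investigators receive only its recommendation.

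Add one sentence stating that the look at about 200 enrolled covers safety and trial conduct and is not a basis for stopping on survival efficacy. If the sponsor does want a survival look, it should be timed by deaths and have a stated boundary. If the full protocol or analysis plan already holds one, a cross-reference is enough.

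The cost is two sentences here and matching text in any committee charter, with no extra patients and no change to the final analysis. The downside is that investigators do not see the interim comparison.

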### Strengths and limitations of this study

The feasibility of ERAS pathway management in improving long-term prognosis has not yet been determined in a prospective RCT. This trial will be the first multicentre randomized controlled clinical trial to evaluate the impact of perioperative ERAS pathway management on the short-term clinical outcomes and long-term prognoses of patients undergoing laparoscopic-assisted radical resection for distal gastric cancer. Jieshou Li, an academician affiliated with the Chinese Academy of Sciences, introduced this concept in 2007. Our centre began to explore ERAS pathway management for patients with gastric cancer during the same year and published RCT research findings on perioperative ERAS management for gastric cancer in 2010 [12]. Our team has accumulated rich experience in perioperative management for gastric cancer to ensure the safety of patients and enhance their recovery. At the same time, our cooperating centres are all members of the gastric cancer ERAS group (each with an annual operation volume of more than 100 cases), have undertaken national clinical projects, and have performed strong clinical research. The primary outcome of this study is the comparison of 3-year OS and DFS between the two groups. The ERAS team will be required to record the data in a timely and accurate manner and to enhance postoperative follow-up in order to avoid loss to follow-up. To this end, we specifically established a data inspection committee and a special follow-up team to ensure the timeliness, validity and authenticity of the clinical data.

In this study, it is expected that owing to individual differences, patient compliance, medical factors and other reasons, the ERAS team will experience some difficulty in completely implementing all interventions in the protocol. We will integrate the elements involved in the clinical pathway. To ensure recovery and reduce hospitalization in the days after gastric surgery, we will pay particular attention to the “key components” of the ERAS programme, namely six basic elements: (1) preoperative patient information and education, (2) preoperative pre-rehabilitation, (3) thoracic epidural anaesthesia combined with multimodal analgesia, (4) target-oriented liquid management, (5) no nasogastric tube, and (6) early oral feeding and mobilization.

## Discussion

The core of the ERAS concept is to use perioperative optimization measures based on evidence-based medicine to reduce surgical trauma and the stress response and to promote postoperative recovery. This concept has subverted the thinking and principles of perioperative management formed over the past hundred years and has created a new concept of rehabilitation. The ERAS pathway not only can improve the early clinical outcomes of patients with gastric cancer but also (it is hoped) can improve the survival rate of patients. This study is a prospective, multicentre, open, randomized controlled clinical trial that aims to provide important evidence support to achieve this goal.

In recent years, many international large-scale gastric surgery centres have begun to explore the ERAS pathway for gastric cancer. The application of the ERAS pathway in the perioperative management of gastric surgery has been repeatedly proven to be able to reduce postoperative complications, shorten postoperative hospital stays, relieve postoperative pain and reduce total hospitalization costs [11, 22]. Unfortunately, the ERAS pathway has limited research on improving the survival of patients with gastric cancer. Current observational studies have shown a significant association between ERAS compliance and colorectal cancer survival. In patients with more than 70% adherence to ERAS interventions, the risk of 5-year cancer-specific death was lowered by 42%, hazard ratio 0.58 (0.39–0.88, Cox regression), compared with all other patients (≤70% adherence) [17]. At present, one mechanism of the ERAS pathway to improve this result is to reduce the surgical stress response [9]. Some studies have shown that perioperative stress not only can affect tumour recurrence [23, 24] but also can stimulate dormant micrometastases and minimal residual cancer [25–27]. In addition, under the ERAS management mode, the immune function after operation can be better preserved. Studies have shown that surgery is related to short-term immunosuppression after surgery [27]. Pro-inflammatory cytokines released after surgery, such as TNF-α and transforming growth factor-beta (TGF-β), have also been shown to stimulate tumour cell adhesion [28, 29]. Patients managed by the ERAS pathway show better preservation of cell-mediated immunity and immune function and a lower stress response, thereby inhibiting tumour recurrence and metastasis and prolonging patient survival [30, 31].

Overall, the ERAS pathway has been proven to be a safe and effective perioperative management model in the recent literature. In particular, the ERAS pathway has shown promising results in improving the survival of patients with gastric cancer. Confirmation of these results is essential by means of RCTs.

## Trial status

The enrolment of this study was ongoing at the time of manuscript submission. The protocol version is 1.1, GISSG18–01, 10 March 2019. The trial will be ongoing from 10 April 2019 to 30 June 2020.

## Data Availability

Data from this randomized controlled study were unavailable at the time of publication. Individual participant data are available upon request.

## Abbreviations

CRF: Case report form
CRP: C-reactive protein
CT: Computed tomography
DFS: Disease-free survival
EN: Enteral nutrition
ERAS: Enhanced recovery after surgery
IL-6: Interleukin-6
OS: Overall survival
POD: Postoperative day
RCT: Randomized controlled trial
TNF-α: Tumour necrosis factor-alpha
